#### Extent of study treatment exposure and compliance

To quantify compliance to the study medication, serum vitamin E levels are measured in all randomized patients before, during (at surgery and 4 weeks postoperatively) and after treatment period. Moreover, patients return their treatment kits to the study site and provide information on their compliance via a short, self-administered questionnaire.

Patients under ACEMg treatment are only classified as compliant (and used for per-protocol analysis):If their vitamin E level 4 weeks postoperatively is ≥20 μg/ml

Nevertheless an ACEMg patient will be classified as noncompliant even though their vitamin E level is ≥20 μg/m if:The patient states in the questionnaire a noncompliance >50 %, and/orThe returned treatment kits contains >50 % of the study medication, whereas missing bottles or blisters are considered as full bottles or blisters

Patients in the placebo group with postoperative vitamin E levels ≥20 μg/ml are most likely to be noncompliant to the study procedures, since they agreed in their informed consent not to use daily multivitamins or other supplements during the course of the study, but show vitamin E levels that are unrealistic without vitamin supplements.

Patients under placebo are classified as noncompliant:If their vitamin E level 4 weeks postoperatively is ≥20 μg/ml, and/orIf the patient states in the questionnaire a noncompliance >50 %, and/orIf the returned treatment kits contain >50 % of the study medication, whereas missing bottles or blisters are considered as full bottles or blisters

### Data handling conventions and missing values

The primary endpoint is residual hearing measured in decibels for a frequency of 500 Hz by air-conducted pure-tone audiometry at the implanted ear. If the patient reaches the upper detection limit of the 500-Hz air-conducted pure-tone audiometry of 110 dB without hearing, the measurement is set to 120 dB as the upper limit of detection + 10 dB. This “upper limit +10” approach is used in all analyses concerning residual hearing (for all frequencies).

The anticipated drop-out rate is expected to be low in PROHEARING as patients in the initial phase after CI are closely followed for clinical reasons. Frequency and reasons for drop-out will be recorded as far as possible and will be analyzed in both study arms. Missing values in the ITT analysis of pure-tone audiometry are replaced by worst possible value, that means that a missing value at any follow-up visit is replaced by the respective upper limit of quantification + 10 dB.

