### Sample size calculation

Sample size is feasibility driven as cochlear implantation with residual hearing is a relatively rare condition. Initial sample size estimation was based on historical data from the MHH Department of Otolaryngology with patients receiving CI electrodes of different lengths. The type-I error was set at 5 % (two-sided) and sample size was calculated for a power of 80 % using a two-group *t* test. A change in hearing thresholds from baseline to 3 months after FF of 15.6 dB with a standard deviation of 15.5 dB at 500 Hz has been observed. For the sample size calculation it has been assumed that the standard deviation is the same in the placebo and in the active treatment group and that the mean change in hearing thresholds is 5 dB smaller with ACEMg therapy compared to placebo. Under these assumptions a required sample size of 150 patients per group was targeted. However, recruitment has been difficult up to now and a total of 300 patients cannot be enrolled in a reasonable time frame. The sample size target was reduced to 70 patients per group in a recent amendment. The power to detect a relevant 5-dB treatment effect decreases to approximately 50 % (which means an increase in the type-II error to 50 %), but a total of 140 patients should be sufficient to decide in this phase II trial whether ACEMg offers a promising treatment concept for protection of residual hearing in CI. The power increases to 80 % if the treatment difference is in the order of 7.5 dB. No interim analysis will be performed.

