### Statistical analysis

The primary analysis is based on the intention-to-treat (ITT) population consisting of all randomized patients who took the study medication at least once. The primary null hypothesis of equal hearing loss in ACEMg and placebo will be evaluated with an analysis of covariance (ANCOVA) model including the factor treatment (ACEMg versus placebo), the baseline residual hearing, surgeon, planned length of electrode and formulation of medication (chewing pills versus softgel capsules). The null hypothesis, of no smaller reduction in residual hearing for ACEMg patients, is rejected if the upper bound of the ANCOVA-derived two-sided 95 % confidence interval of the difference in change from baseline (ACEMg minus placebo) is less than 0.

To evaluate the robustness of the estimated treatment effect, the primary analysis will be repeated based on the per-protocol population. In addition, the primary objective is evaluated with the nonparametric, stratified Gehan test as a sensitivity analysis. Moreover, analysis will be conducted using real length of electrode instead of planned length of electrode as independent factor.

Secondary analyses will be conducted on the ITT population and on the per-protocol population as sensitivity analyses. Key secondary analyses include the comparison of ACEMg group to placebo in terms of residual hearing for different frequencies and different timepoints after surgery. All analyses will be performed in line with the primary analysis using ANCOVA. Differences in the treatment effects within patient groups with different electrode length are evaluated descriptively.

Absolute and relative frequencies of (serious) adverse events will be listed for each treatment group separately. Differences will be analyzed in a descriptive manner. The safety population will be used for analysis.

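### Worst-value replacement of every missing threshold in the primary analysis is not conservative: it can bias the result either way, and it lowers power unless missingness is very low or baselines lie near 95 dB

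*Protocol article*

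**What the plan says.** All references are to the protocol article.

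- **Missing data** (Data handling conventions and missing values): in the ITT analysis of pure-tone audiometry, "a missing value at any follow-up visit is replaced by the respective upper limit of quantification" plus 10 dB. The same section sets a 500 Hz test without response at the 110 dB limit to 120 dB. A missed visit and a measured no-response therefore receive the same number. Drop-out is expected to be low, without a figure, and its frequency and reasons will be analysed by arm.
- **Analysis set** (Statistical analysis): the primary ANCOVA uses the ITT population, "consisting of all randomized patients who took the study medication at least once".
- **Sample size** (Sample size calculation): planning rests on historical data from the study department, namely "A change in hearing thresholds from baseline to 3 months after FF of 15.6 dB"; the SD is taken as 15.5 dB in both arms. The original target assumed that "the mean change in hearing thresholds is 5 dB smaller with ACEMg therapy compared to placebo". With 70 per group, power is given as 80% "if the treatment difference is in the order of 7.5 dB". No allowance is made for missing values or for the replacement rule.
- **Robustness** (Statistical analysis): a per-protocol repeat, a stratified Gehan test, and a repeat with actual electrode length.

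**The concern.** The rule takes no account of why a value is missing or of what the neighbouring visits show. The study calendar (Table 5) schedules unaided audiometry at days 1–5, at first fitting and at months 3, 6, 9 and 12. A patient with preserved hearing at first fitting and at month 6 who misses month 3 is still analysed as having no measurable hearing at 500 Hz at the primary time point. The better the baseline hearing, the larger the loss assigned.

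Worst-value replacement is often regarded as cautious. It would be cautious if it counted only against the active arm, but here it applies to both arms, so its direction follows whichever arm has more missing audiograms. The primary estimate then mixes hearing loss with visit attendance. The large imputed losses also widen the residual spread, and equal missingness shrinks the difference between arms.

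Read literally together with the one-dose ITT definition, the rule would also cover a patient who starts medication two days before surgery and is then not implanted.

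**Working it through.** **Inputs from the article.** 70 per arm, 1:1; two-sided 5%; mean change 15.6 dB (taken as the placebo mean); SD 15.5 dB in both arms; baseline at 500 Hz no worse than 95 dB; replacement value 120 dB.

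**Assumptions, because the article gives no figure.** Mean baseline B from 60 to 95 dB; share missing q from 1% to 10% per arm, unrelated to outcome.

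**Step 1: reproduce the stated figures.** SE = 15.5 × √(2/70) = 2.62. Power at 7.5 dB = Φ(7.5/2.62 − 1.96) = 81.7% (81.1% with the t distribution), so the stated 80% reproduces. For 5 dB and 80% power, n = 2 × (1.96 + 0.8416)² × 15.5²/5² = 150.9, that is 151 per arm against the 150 stated.

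**Step 2: size of the imputed loss.** Loss = 120 − B: 25 dB at B = 95, 35 at 85, 45 at 75, 60 at 60. The planned mean is 15.6 dB.

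**Step 3: power with equal missingness.** For an arm with mean m among observed patients:

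- mean = (1 − q)m + q(120 − B)
- variance = (1 − q) × 15.5² + q(1 − q)(m − (120 − B))²

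Example with B = 75, q = 5%, true benefit 7.5 dB:

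- ACEMg mean = 0.95 × 8.1 + 0.05 × 45 = 9.95; variance = 228.2 + 0.0475 × 36.9² = 292.9
- Placebo mean = 0.95 × 15.6 + 0.05 × 45 = 17.07; variance = 228.2 + 0.0475 × 29.4² = 269.3
- Difference 7.12 dB; SE = √((292.9 + 269.3)/70) = 2.83; power = Φ(7.12/2.83 − 1.96) ≈ 71%

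Power at 7.5 dB over the grid:

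| Baseline | 1% | 2% | 5% | 10% |
|---|---|---|---|---|
| 60 dB | 77.6% | 73.7% | 62.9% | 49.0% |
| 75 dB | 79.5% | 77.4% | 71.0% | 61.2% |
| 85 dB | 80.4% | 79.1% | 75.3% | 68.8% |
| 95 dB | 81.0% | 80.3% | 78.2% | 74.4% |

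Simulated ANCOVA (treatment and baseline, with baselines varying between patients and truncated at 95 dB, mean before truncation 60 to 85 dB) gives somewhat lower values: about 72–80% at 1–2% missing, 60–73% at 5% and 46–64% at 10%.

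**Step 4: how much is the rule and how much is lost data.** Analysing observed patients only, the formula gives 79.7% at 5% missing and 77.5% at 10%; simulation agrees at about 77–80%. Nearly all the loss in Step 3 therefore comes from the replacement.

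**Step 5: unequal missingness, no true effect.** Spurious benefit = (q placebo − q ACEMg) × (120 − B − 15.6). For 3% ACEMg against 8% placebo: 0.05 × 44.4 = 2.2 dB at B = 60, 0.05 × 29.4 = 1.5 dB at 75, 0.05 × 19.4 = 1.0 dB at 85. The ANCOVA simulation gives about 1.2–2.3 dB and about 6–10% false ACEMg wins against 2.5%. Its lower end is above 1.0 because truncation pulls the mean baseline below 85 dB.

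**Step 6: unequal missingness, true benefit 7.5 dB.** With 10% missing on ACEMg and 5% on placebo at B = 60: placebo mean 0.95 × 15.6 + 0.05 × 60 = 17.82, ACEMg mean 0.90 × 8.1 + 0.10 × 60 = 13.29, estimated benefit 4.5 dB. At B = 75 it is 5.3 dB; the simulated range is about 4.5–5.7 dB. Power is 27% at B = 60 and 43% at B = 75. The reverse imbalance inflates the estimate to 9.3 and 8.6 dB.

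**The case against.** **Low drop-out.** The article expects little drop-out because patients are closely followed for clinical reasons. At 1–2% missing the loss of power is modest, and with baselines near 95 dB it is small even at 5%. A reader might infer that the rule simply removes the 80% power. The documents do not support that: the loss depends on a missing rate and a mean baseline that are not given. If placebo has more missing values, power is even kept, though through bias.

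**Blinding.** Products look identical, few adverse events are expected, and patients who stop medication may stay in follow-up. No mechanism for a large imbalance is evident, and equal missingness does not raise the type I error. This stands, and the imbalance figures are illustrations of sensitivity, not forecasts.

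**Other safeguards.** The replacement is stated only for the ITT analysis, a per-protocol repeat is planned, the Gehan test is rank-based and so limits the pull of extreme values, and drop-out is analysed by arm. These help interpretation but do not repair the primary estimate. None is described as an alternative treatment of missing values, and the per-protocol set is selected on compliance and vitamin E levels after randomization.

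**Never-implanted patients.** The endpoint is defined at the implanted ear, and the article does not say how such a patient is scored. That they would be given the worst value is a literal reading of two sections together, not a stated rule, and few cases are likely.

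**Wording.** It would also be too strong to say that the rule codes total deafness. It codes no measurable hearing at each missing frequency.

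**Conclusion.** The point holds in conditional form. Worst-value replacement is fixed in the article for the primary analysis, so it is not a detail left to an unseen analysis plan. It treats absent data as the worst observation, disregards adjacent audiograms, and is not conservative. The bias under the null is about 0.3 dB per percentage point of imbalance at a baseline of 75 dB and 0.44 dB at 60 dB. The stated power is correct for complete data. It is nearly preserved under the rule only if missingness is very low or baselines lie near the 95 dB limit, and the article establishes neither. All sizes rest on the assumed baselines and missing rates and on missingness unrelated to outcome. Severity: should fix. Low expected drop-out and an openly feasibility-driven phase II sample size argue against a higher rating.

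**What to change.** 1. Keep 120 dB only for a measured no-response at the audiometer limit.
2. Make the primary analysis a missing-at-random method that uses all observed visits: a mixed model for repeated measures, or multiple imputation followed by the same ANCOVA.
3. State how patients who were dosed but never implanted are handled, and do not score them as worst loss.
4. Retain worst-value replacement as a sensitivity analysis.
5. If the rule stays primary, restate the power in the sample size section with the rule included, over a stated range of missingness and baseline.

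The cost is protocol and analysis-plan wording and a little programming, with no new patients or measurements. The trial statisticians remain blinded until the blind data review, so the change can be made before unblinding. The drawback is reliance on a missing-at-random assumption that the data cannot confirm; the retained worst-value analysis probes it.

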### Data management

All study data are collected by study personnel. Data are entered via an eCRF in a clinical trial database. For each patient enrolled an eCRF must be completed after the patient’s visit. This also applies to records for those patients who fail to complete the study. Only SAEs will be additionally documented and notified on paper forms.

Verification of the data in the eCRF occurs by monitoring as well as via range, validity, and consistency checks programmed in the system. In certain cases, queries can be detected by the study software or by an authorized study staff member. Based on the queries, the investigator can review and answer the discrepancies that are found directly in the system. All changes of data entered in the eCRF can be followed by an audit trail.

A quality control will be performed before the database is closed. This procedure is documented. After the close-out visit at the study center the access of the investigator to the eCRF/database is changed to a “read-only” access (modification of data is no longer possible). After database closure the investigator and the data manager can only read the data, they can not change them; the final data set is transferred to the Institute for Biometry for statistical analysis of the SAS data.

### Patient information/informed consent and data protection

The investigator is responsible for obtaining the patient’s written informed consent after adequate explanation of the aim, study assessments, potential risks, benefits, and consequences of the study, as well as alternative treatment options. The patient information/informed consent form has to be signed in duplicate by the patient and the investigator. One document will be given to the patient, the other remains in the Trial Investigator File (TIF) at the trial site. No study procedures are allowed to be conducted until the patient’s written informed consent has been obtained.

The patient information/informed consent form has to be revised whenever important new information becomes available that may be relevant to the subject’s consent. The patients have to be informed and asked to give their consent to continue study participation by signing the updated form.

All study staff members have to give due consideration to data protection and medical confidentiality. The collection, transfer, storage and analysis of personal study-related data are performed pseudonymized according to national regulations. The declaration of data protection is contained within the patient information/informed consent form.

### Monitoring and audits/inspections

To ensure compliance with the protocol, to legal and regulatory requirements applicable for clinical trials and with the ethical principles of the Declaration of Helsinki and the International Conference on Harmonization of Technical Requirements for Registration of Pharmaceuticals for Human Use (ICH) and GCP, monitoring visits are scheduled to take place during the study. At those regular monitoring visits, the monitor reviews the eCRF for completeness and clarity and performs source data verification. Source data are defined as any printed, optical and electronic document containing source data (e.g., hospital records, laboratory notes, drug accountability records). The monitor also reviews notification of SAEs and the TIF.

Audits (by the sponsor) and inspections (by regulatory authorities) may be performed in order to verify that the clinical study is performed according to the study protocol as well as to other applicable regulatory requirements. The auditor or inspector is independent in regard to personnel involved in the conduct of this clinical trial. This may occur at any time from start to after closure of the study.

Generally the sponsor quality manager audits the conduct of a clinical trial on a regular basis (determination of frequency is risk-adapted; usually annually). Inspections by regulatory authorities happen infrequently and cannot be foreseen by the investigator or sponsor.

The establishment of a data monitoring committee (DMC) for this clinical study was not considered necessary by the sponsor as a “non-critical indication where patients are treated for a relatively short time and the drugs under investigation are well characterized and known for not harming patients” (cited from “Guideline on data monitoring committees,” EMA 27 July 2005) is being investigated. In addition, safety endpoints are verified by the monitor during periodic monitoring visits and reported to the sponsor within the written report after each visit.

## Discussion

The insertion of a CI into the inner ear is to some extent potentially damaging to the inner ear tissue, which can affect the endocochlear potential, create oxidative stress, and initiate proapoptotic pathways associated with direct injury to, and loss of, hair cells [11]. Even though to our knowledge the exact mechanisms involved during CI surgery that results in loss of residual hearing are not completely understood recent findings on caspase activation, JNK activation, oxidative stress with reactive oxygen species, and lipid peroxidation of cellular membranes [12] give a first hint of possible targets for drug-based therapies of insertion trauma-related hearing loss.

There is an increasing role for antioxidants in the protection of residual hearing loss as there is more evidence that links high levels of oxidative stress to programmed cell death of the remaining hair cells. Knowledge of the mechanisms underlying noise-induced hearing loss (NIHL) and drug-induced hearing loss (DIHL) has led to the hypothesis that cochlear-implantation-related hearing loss is based on the same pathophysiology. Noise and ototoxic drugs induce free radical formation in the inner ear, which up-regulate apoptotic cell-death genes [13]. If free radical build up is sufficient, cell membranes are attacked, resulting in necrotic cell death [13].

Some exogenous antioxidants were tested in animal models and some degree of benefit has being shown against cisplatin, carboplatin, aminoglycoside, and noise-induced trauma to the inner ear: D-methionine (D-met [14]); ascorbic acid (vitamin C [15]); *dl*-α-tocopherol (vitamin E [16]); *N*-acetylcysteine (NAC [17, 18]). Clinical trials examining the benefit of antioxidants on hearing loss of different origins are various and include NAC (ClinicalTrials.gov Identifier: NCT00552786), NAC + Mg (ClinicalTrials.gov Identifier: NCT01727492) or ACEMg (ClinicalTrials.gov Identifier: NCT00808470), which has been evaluated for the treatment of NIHL. NAC (ClinicalTrials.gov Identifier: NCT02094625) has been tested for the prevention of cisplatin-induced hearing loss or sodium thiosulfate to prevent carboplatin- [19] or cisplatin-induced hearing loss (ClinicalTrials.gov Identifier: NCT01369641; ClinicalTrials.gov Identifier: NCT00716976; ClinicalTrials.gov Identifier: NCT02281006). Prevention of drug-induced ototoxicity is being tested by NAC treatment (ClinicalTrials.gov Identifier: NCT01131468). But, to our knowledge, only one study has addressed hearing loss associated with electrode insertion trauma and cochlear implantation. In this study the researchers were able to demonstrate benefit with NAC treatment [17]. This benefit only pertained to the high frequencies of the basal turn and did not extend significantly to low-frequency hearing located in the apical section of the cochlea [17]. Unfortunately, delivery of NAC to the round window prior to implantation caused a slight increase in hearing thresholds and greater amounts of osteoneogenesis, which may preclude its use locally in the protection of residual hearing [17]. However, there have been no randomized controlled trials to investigate antioxidant effects on CI electrode-insertion-related hearing loss. The study protocol of this clinical trial allows controlling of all parameters influencing residual hearing after cochlear implantation. Performing all surgeries and patient follow-up at one study side leads to maximum consistency in diagnostics and therapy by there being less variability in surgery and audiological testing techniques and fitting. This approach will allow a better detection of the influence of ACEMg on residual hearing in CI patients.

The dosage of vitamin C (magnesium ascorbate; 500 mg), magnesium (magnesium citrate, magnesium ascorbate, magnesium stearate; 315 mg), vitamin E (*dl*-α-tocopherol acetate; 267 mg), and β-carotene (18 mg) administered in this placebo-controlled trial was chosen to find the correct balance between a potential therapeutic effect and the suggested tolerable upper intake level: the maximum level of total chronic daily intake of a nutrient (from all sources) judged to be unlikely to pose a risk of adverse health effects to humans [20].

If the hypothesis that decreasing free radicals with this formulation of micronutrients will preserve residual hearing in CI patients is correct, then these patients will benefit from better hearing sensation.

